### Study Outcomes

The primary and secondary outcomes are summarized in Table 1. Data will be collected either from the electronic medical record (EMR), the HIV database, or directly from the participants’ responses to questionnaires. For analysis, all outcomes (Table 1) will be reported as a change from baseline. As this is a pilot study, our intention is to determine the most sensitive measures. We will explore the data to determine the most suitable categorizations for a future study; therefore, the total scores will be reduced to categories once all data have been compiled. To report on the participant characteristics, sociodemographic data, including age, race/ethnicity, HIV or AIDS status, socioeconomic status, pregnancy status, substance use, and mental health history (past year), will be collected at T0.

Clinical outcomes (at T0, T1, and T2) that will be examined include a comparative history of self-reported medication adherence, visit attendance, and viral suppression reported as the biological marker of HIV viral load (copies/mL). Psychological and behavioral data include depressive symptoms, internalized stigma, resilience, and medical mistrust (Table 1).

### Power Analysis

This study aims to develop and measure the feasibility of a pilot system. Therefore, a power analysis is not appropriate for this study. The plan is to estimate the expected effect sizes and determine the sensitivity of the measures at the conclusion of the study.

### Recruitment Strategy

Participants will be enrolled from a women’s HIV service in an academic medical center where approximately 900 individual women are seen annually. An estimated 50 patients are seen weekly. The women’s HIV service is made up of a variety of clinics, including prenatal, primary care, and gynecological specialty care. The women’s HIV service collects sociodemographic information, appointments, and laboratory/pathology results in its database (Ryan White Care Ware system) to comply with the reporting and quality requirements of its various funding sources. Information such as missed appointments, adherence to medication, viral load, primary language spoken, and ethnic/racial background will be extracted from the Ryan White Care Ware system for all potential study participants with a confirmed appointment.

### Assignment to Study Arms

Participants will be randomized 1:1 to 1 of the 2 treatment arms. Randomization will be stratified by language, where approximately 10 participants per language group will be enrolled in each study arm. This ensures that approximately equal numbers of participants by language groups are represented in each study arm. A randomization schedule will be created by the study statistician based on the Excel function of random number generation. The randomization schedule will be of a randomized block nature to ensure relative equality of assignment across conditions and to prevent the potential of study staff guessing the next assignment. Randomization will take place upon the completion of baseline assessments. The study group assignment will be communicated back to the study team member who consented the patient within 24 hours of enrollment.

### Data Collection, Management, and Analysis

#### Data Collection Plan

##### Qualitative Component

Audio recordings gathered from all qualitative data (FG1, FG2, KI1, and KI2) will be transcribed using a commercially available transcription software available in English and Spanish. In addition, 2 study team members will review the entire transcription and make changes manually through the software. The Haitian Creole audio will be transcribed manually. The transcripts, along with other information (see Instrumentation), will be entered into a software package designed for mixed methods analyses [27].

##### Quantitative Component

Unless stated otherwise, all data will be collected at T0, T1, and T2. Participants will complete their paper forms. All questionnaires are meant to be self-administered, but a research team member will be present at all times to answer any questions that the participant may have.

##### Quantitative Data Sources

Data will be collected from the clinic’s EMR, the women’s HIV service database, and directly from the participants.

#### Instrumentation

##### Sociodemographic, Clinical, and Behavioral Data

Demographic, behavioral and mental health history, and clinical data outcomes, including viral suppression and visit history, will be extracted from the EMRs for each participant. Demographic data will be collected at the time of consent for both the qualitative and quantitative studies.

##### Background, Financial Information, and Viral Suppression (Self-Reported)

Self-reported sociodemographic information, including age, race/ethnicity, place of birth, marital status, relationship status, highest level of education completed, employment status, annual income, adherence to medication, viral load, and CD4 count, will be collected.

##### Three-Item Self-Report Measure for Medication Adherence

Medication adherence will be measured using the 3-item self-report measure for medication adherence, which examines *days taken*, *frequency*, and *rating of medications* over the past 30 days. This questionnaire has been validated using an electronic drug monitoring device (Cronbach α=.84 for HIV antiretroviral medications) [16]. The questionnaire was translated into Spanish and Haitian Creole and will be piloted with FG1 participants.

##### HIV Stigma Scale

Internalized stigma will be measured using the HIV-related stigma scale, a 40-item measure validated in both English (Cronbach α=.96) [20] and Spanish (Cronbach α=.91) [21]. Individuals rate statements such as “Some people act as if it’s my fault I have HIV” on a 4-point Likert-type scale (*1=strongly disagree* to *4=strongly agree*). The scale will be translated into Haitian Creole and then piloted with the FG1.

##### Group-Based Medical Mistrust Scale

Medical mistrust will be measured by the group-based medical mistrust scale, which comprises 12 items (Cronbach α=.64-.70), with statements such as “I have personally been treated poorly or unfairly by doctors or health care workers because of my ethnicity” rated by patients on a 5-point Likert-type scale (*1=do not agree at all* to *5=completely agree*) [22]. It has been translated and validated into Spanish (Cronbach α=.80) [23]. A Haitian Creole version has been created and will be piloted with FG1 participants.

##### Resilience

The Connor-Davidson resilience scale (CDRISC-25) is a validated 25-item questionnaire (Cronbach α=.89), including statements such as “When things look hopeless, I don’t give up,” and responded to on a 5-point Likert-type scale (*0=not true at all* to *4=true nearly all of the time*) [24]. The CDRISC-25 has been translated and validated in Spanish (Cronbach α=.89) [25] and in Haitian Creole (Cronbach α=.80) [26].

##### Patient Health Questionnaire-9

Depressive symptoms will be measured using the Patient Health Questionnaire-9. Participants will rate the questionnaire on a 3-point Likert-type scale based on how often they have been bothered by any of the symptoms stated (*0=not at all* to *3=nearly every day*). It has been validated in English (Cronbach α=.89) [17], Spanish (Cronbach α>.89) [28], and Haitian Creole (Cronbach α=.78) [19].

#### Data Management

The completed questionnaires will be stored in a secured cabinet in a locked room inside the PI’s office. Only the PI and study team members will have access to the data forms and electronic versions of the collected data. Data will be extracted from the paper surveys and entered into an HIPAA-compliant database. Deidentified data will be exported into file formats appropriate for analysis. Authorized team members will use their unique password-protected accounts to access the database. A master spreadsheet will be available to all study team members, uploaded into a *cloud* document manager, and the participant’s study ID number will be recorded. This spreadsheet will be encrypted and will be the only database that contains identifying information. All data collection forms, consent forms, and the study log will be stored for 3 years after the closure of the study. The audio and transcription files will also be stored in the *cloud* document manager.

### Study Outcomes

#### Qualitative Data Analyses

Recordings from FG1, FG2, KI1, and KI2, for both the English and Spanish languages, will be processed using a commercially available transcription software and reviewed by a study team member fluent in that language. Haitian Creole will be transcribed manually. All transcriptions will be reviewed a second time by a different study team member fluent in the language. Spanish and Haitian Creole language texts will be first translated into English. The English texts will be analyzed iteratively for thematic content (major themes). Themes pertaining directly to the research questions will inform the mHealth system customization. Dedoose [27] mixed methods analysis software will facilitate data analysis. Overall, 2 study team members will review, enhance, and categorize the software-generated codes. A codebook will document each iteration of the data analysis.

#### Quantitative Data Analysis

##### Data Preparation

###### Sociodemographic and Clinical Data

Participants’ mobile numbers will be matched to the mHealth texting system logs; participants’ medical record number (MRN) will be matched to the Ryan White Care Ware database and the hospital’s EMR. Inconsistent data and outliers will be reviewed. Missing data and unresolved data discrepancies will be considered and recorded as *missing data* and excluded from the analyses.

###### Study Measures

Questionnaires will be evaluated and compared with the expected response ranges. Participant-level records with incomplete responses will be considered missing for all instruments.

##### Descriptive Statistics

Groups (intervention vs control) will be compared by baseline characteristics to detect significant group differences, (eg, chi-square values and odds ratios for frequency tables and *t* tests for continuous variables). Cutoffs at *P*<.05 will determine 2-tailed significance. If needed, an alternate (Fisher exact test) or a nonparametric analysis will be conducted.

##### Exploratory Analyses

We will conduct exploratory analyses, where analysis of variance (ANOVA) models will be constructed for each outcome variable. Statistically significant baseline characteristics, mHealth usage, clinically relevant characteristics, and total instrument score will be entered as covariates. The ANOVAs will compare T1 and T2 outcomes to values at T0 by the study group. At T1 and T2, clinical and behavioral outcomes will be compared with values at T0 for both study arms.

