### Trial Design

This is a concurrent, two-phase, mixed method, pilot randomized controlled trial. Both the qualitative and quantitative components collect data from the target population women living with HIV. The trial begins with the qualitative component.

#### Phase 1

The qualitative component comprises interviews in the form of participant focus groups and participant key informant sessions.

#### Phase 2

The quantitative component is a short-term longitudinal intervention, where participants will be randomized to 1 of 2 study arms (parallel group). The allocation ratio is set at 1:1. The control arm will receive the standard of care for reminders, and the experimental arm will receive the intervention, in addition to the standard of care for reminders (see Study Comparators section). Data will be collected at baseline (T0), 3 to 4 months postbaseline (time 1; T1), and 6 to 9 months postbaseline (time 2; T2) after the launch of the intervention (exploratory trial).

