**Secondary outcomes**								
	**Clinical outcomes**							
		Adherence to medication		Wilson 3-item self-report measure for medication adherence (self-administered) [16]		Continuous (score); range 1-100		Participant (T0, T1, and T2)
		Clinic attendance (change)		Number of missed visits 1 year before assessment (T0), between T0 and T1, and between T1 and T2		Continuous (number)		Electronic medical record
		Viral suppression		Viral load		Categorical; ≥20 copies/mL or <20 copies/mL		Electronic medical record or measured through a blood test (T0, T1, and T2)

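### Missed visits are counted over 12, 3–4 and 2–6 months and compared raw with T0, so both arms appear to improve even if nothing changes

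*Protocol article*

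**What the plan says.** Under Exploratory Analyses the article states that "analysis of variance (ANOVA) models will be constructed for each outcome variable". Two comparisons follow. The first is of change between groups: "The ANOVAs will compare T1 and T2 outcomes to values at T0 by the study group". The second sets each arm against its own baseline: "At T1 and T2, clinical and behavioral outcomes will be compared with values at T0 for both study arms". The Study Outcomes section fixes the reporting scale: "For analysis, all outcomes (Table 1) will be reported as a change from baseline".

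Table 1 defines clinic attendance as "Number of missed visits 1 year before assessment (T0), between T0 and T1, and between T1 and T2" and types it as a continuous number. Trial Design places T1 at 3 to 4 months and T2 at 6 to 9 months after baseline. Viral suppression, another clinical outcome in the same table, is typed as "Categorical; ≥20 copies/mL or <20 copies/mL".

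The only fallback, "If needed, an alternate (Fisher exact test) or a nonparametric analysis will be conducted", stands under Descriptive Statistics, which concerns the comparison of baseline characteristics.

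**The concern.** The three attendance counts cover different lengths of time. A year offers more chances to miss a visit than three or four months, so a raw difference between a follow-up count and the T0 count mixes any change in behaviour with the change in window length. The article plans exactly that difference, in both arms, and mentions neither a rate, nor scheduled visits as a denominator, nor follow-up time.

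Two things are at stake. Read arm by arm, both groups would seem to miss far fewer visits after enrolment. And the Power Analysis section says that the study is meant to yield expected effect sizes and show which measures are sensitive. An attendance measure built this way does both jobs badly.

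**Working it through.** The article states no power, effect size or missed-visit rate, so there is no figure of its own to reproduce. The window lengths come from the article; everything marked as assumed does not.

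**Windows**
- T0: 12 months (Table 1).
- T0 to T1: 3 to 4 months (Trial Design).
- T1 to T2: shortest 6 − 4 = 2 months, longest 9 − 3 = 6 months.

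**Apparent change with a constant rate.** Expected count = yearly rate × window / 12. The rate cancels in the ratio to T0:

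| Window | Ratio to T0 | Apparent fall |
|---|---|---|
| T0–T1, 3 months | 3/12 = 0.25 | 75% |
| T0–T1, 4 months | 4/12 = 0.33 | 67% |
| T1–T2, 2 months | 2/12 = 0.17 | 83% |
| T1–T2, 6 months | 6/12 = 0.50 | 50% |

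Expressed per month, each ratio is 1.0.

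**Would a test against T0 notice?** Target Sample Size gives about 20 women in each of 3 languages, half of them controls: 60 in all, 30 per arm. Assume 2 missed visits a year, a 3.5-month window and gamma-Poisson variation between women with shape 3.
- T0 count: variance 2 + 2²/3 = 3.333.
- Follow-up count: mean 2 × 3.5/12 = 0.583; variance 0.583 + 0.583²/3 = 0.697; SD 0.83.
- Covariance: 2 × 0.583/3 = 0.389.
- Change: mean 0.583 − 2 = −1.417; variance 3.333 + 0.697 − 2 × 0.389 = 3.252; SD 1.80.
- Standard error in one arm: 1.80/√30 = 0.33, so the spurious change is about 4.3 standard errors from zero.

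A simulation of 40,000 runs agrees: the within-arm test rejects in 99.6% of runs with no true change. With assumed rates of 1, 2 or 4 a year and shape 1 or 3, false rejection is 89–100% for a 3.5-month window and 54–100% over windows of 2, 3.5 and 6 months, against a nominal 5%.

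**Between arms, equal windows.** The spurious fall is the same in both arms and cancels. Simulated type I error is 4.6–5.1% on change and 4.6–4.9% on the follow-up count, with null estimates near zero.

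**Noise in the raw change.** Suppose the intervention halved the rate in the scenario above. The expected difference between arms is 0.583/2 = 0.292 visits. Divided by the control-arm SD, that is 0.292/1.80 = 0.16 on change but 0.292/0.83 = 0.35 on the follow-up count. Simulated power is 9% and 34% respectively.

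**Viral suppression by ANOVA, between arms.** At 30 per arm with assumed suppression of 50–90%, type I error is 4.7–5.4%. A true risk difference of 0.20 is estimated as 0.200–0.201. Coverage of the 95% interval over all scenarios is 94.5–95.3%. In one illustrative model with covariates, about 7.5% of fitted values fell outside 0 to 1.

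**The case against.** A reader might infer something stronger: that prescribing ANOVA for a binary outcome and a count makes the estimates and standard errors wrong for two of the three clinical outcomes. The documents do not support that. For suppression, ANOVA between arms estimates a difference in proportions, and the check above finds it unbiased with near-nominal coverage. A claim that a pooled error term badly distorts the standard errors would need an error pooled over the three time points, and the article does not specify the structure of the ANOVA. For attendance, ANOVA is not the cause: a Poisson model without an offset would show the same fall.

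It can also be said that the models are labelled exploratory, that the primary outcomes are feasibility and acceptability, and that the randomised contrast is protected. The Abstract mentions chi-square tests and odds ratios by study group without confining them to baseline. And if the T0 count were entered as a covariate, most of the noise in the change score would go.

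Most of this stands and limits the point. It does not remove it. The comparison of each arm with T0 is planned in so many words, and a nonparametric fallback would not correct unequal windows even if it extended to the outcome models. The covariate list does not name the T0 value of the outcome. Exploratory status is no defence when effect sizes are what the pilot is meant to deliver. Protection of the between-arm contrast also depends on equal windows: T1 and T2 are tied to clinic visits and the intervention sends reminders, so window length could differ by arm. That is a risk, not something the article shows to happen.

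**Conclusion.** The point holds for missed visits compared with T0. With a constant underlying rate, the planned raw comparison shows a fall of 67–75% at T1 and 50–83% at T2 in both arms. Those figures need only the article's visit times and the constant rate. The false-rejection and power figures also rest on assumed rates and assumed variation between women.

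The between-arm contrast is unbiased if windows match by arm, but as a raw change it is inefficient, and attendance could wrongly be judged an insensitive measure. For viral suppression there is only a mismatch between model and scale, not a demonstrated error in the arm comparison. The matter concerns a secondary outcome in a pilot and should be corrected before analysis.

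**What to change.** For attendance, replace the raw count with one of two analyses: missed visits out of scheduled visits (binomial), or a Poisson or negative binomial model with a log scheduled-visits or log follow-up-time offset. Compare arms at T1 and at T2, adjusting for the T0 rate and for language, the stratification factor. Report any change from T0 as a change in rate. Leave conclusions about the intervention to the between-arm comparison: missed visits are one route into the trial under Eligibility Criteria, so rates may drift after entry without any treatment effect. Tabulate window length by arm.

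As a minor change, name a binary-data model for viral suppression in place of ANOVA: logistic regression, or a risk difference with confidence interval, adjusted for T0 suppression and language.

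The cost is analysis wording. Recruitment Strategy says that the clinic database already holds appointments, and eligibility already uses scheduled visits, so no new data collection should be needed.

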**Methods:**

Women (age ≥18 years) who were followed up at the women’s HIV clinic of an academic medical center, with a recent history of nonadherence to HIV care (missed appointments, unsuppressed viral load, or not taking medications as prescribed), will be enrolled. The experimental arm will receive the intervention, which includes health reminders and psychoeducational messaging, plus clinical standard of care reminders. The psychoeducational messaging will target patient-level barriers of HIV stigma and medical mistrust and resilience as a patient-level strength. The control arm will receive standard of care reminders only (ie, mailed appointments and automated telephone calls). All aspects of the study and intervention will be offered in the participants’ preferred language. The primary outcome is the feasibility and acceptability of the study. The secondary outcomes are changes in self-reported medication adherence, depression symptoms, HIV stigma, medical mistrust, resilience, and clinic attendance and viral suppression extracted from the participants’ medical records. Data will be assessed at baseline (T0) and 2 subsequent clinic visits—approximately 3 to 4 months from the baseline (time 1; T1) and 6 to 9 months from the baseline (time 2; T2). Qualitative data will be transcribed and analyzed iteratively. Bivariate analyses will compare data by the study group (chi-square, odds ratios, and t tests). Exploratory analyses will be conducted for each outcome variable—T1 and T2 values will be compared with values at T0 by the study group.

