	**Acceptability of the mobile health app**							
				The proportion of messages opened out of the number of messages received		Continuous; range 0-1		Data usage logs (T0, T1^b^, and T2^c^)

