##### Statistical Analysis: Missing Data

For individual statistical tests, only records with complete data will be included in the analyses.

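### Message usage, which arises after randomisation and is undefined for controls, is entered as a covariate in the exploratory between-arm models, so their arm effect is either not estimable or not the randomised contrast

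*Protocol article*

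**What the plan says.** All references are to the protocol article.

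- **Model.** Under Exploratory Analyses: "We will conduct exploratory analyses, where analysis of variance (ANOVA) models will be constructed for each outcome variable". The comparison is by arm: "The ANOVAs will compare T1 and T2 outcomes to values at T0 by the study group".
- **Covariates.** The same paragraph states: "Statistically significant baseline characteristics, mHealth usage, clinically relevant characteristics, and total instrument score will be entered as covariates". Nothing there limits usage to one arm or to a separate model.
- **Usage measure.** Table 1 defines one quantity, under acceptability of the app: "The proportion of messages opened out of the number of messages received". It is taken from the texting system's logs.
- **What each arm receives.** The abstract's Methods say: "The control arm will receive standard of care reminders only (ie, mailed appointments and automated telephone calls". Trial Design (Phase 2) says "the experimental arm will receive the intervention, in addition to the standard of care for reminders".
- **Timing.** Assignment to Study Arms places randomisation after the baseline assessments.
- **Missing data.** Under Statistical Analysis: Missing Data: "only records with complete data will be included in the analyses".

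The article does not say what usage value a control participant is given.

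**The concern.** A covariate in a randomised comparison should be fixed before allocation. Usage in the trial is a consequence of allocation: one arm is sent messages and the other is not. Conditioning on it replaces the comparison that randomisation protects with a different one, and here the covariate does not exist in one of the two arms.

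What is at stake is the arm comparison of the secondary outcomes over time (self-reported adherence, missed visits, viral suppression, depressive symptoms, stigma, mistrust, resilience). Power Analysis says that effect sizes will be estimated at the end of the study, and Conclusions presents the study as the basis for a larger trial. An arm effect taken from these models for that purpose would mislead its planners.

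**Working it through.** **Inputs from the article.** About 20 participants per language in 3 languages, half of them controls (Target Sample Size), and about 10 per language per arm (Assignment to Study Arms): 3 × 20 = 60 in total, 3 × 10 = 30 per arm. The article states no effect size, power or usage distribution, so there is no figure of its own to reproduce.

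**Assumptions.** Outcome SD of 1, true effects of 0 or 0.8 SD, and the usage means and SDs shown below.

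**Step 1: control usage left missing.** Messages opened over messages received is 0/0 for a control. Under the complete-record rule, 60 − 30 = 30 records remain, all from the intervention arm. The arm column then equals the intercept column. The design matrix (intercept, arm, usage) has rank 2 of 3, so the arm effect is not estimable.

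**Step 2: control usage coded 0.** Write the model as y = a + b·arm + c·usage. Controls all have usage 0, so they fix only a. The arm coefficient b is the intervention-arm regression line at usage 0 minus the control mean. The randomised contrast is b + c·m, with m the mean usage in the intervention arm. The two coincide only if c = 0.

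**Step 3: precision.** With equal arms and usage mean m and SD s in the intervention arm, R² between arm and usage = (m/2)² / [(m/2)² + s²/2], the variance inflation factor (VIF) = 1/(1 − R²), and the standard error is multiplied by √VIF.

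| m, s (assumed) | R² | VIF | SE multiplier |
|---|---|---|---|
| 0.7, 0.20 | 0.1225/(0.1225 + 0.0200) = 0.86 | 7.1 | 2.7 |
| 0.5, 0.25 | 0.0625/(0.0625 + 0.03125) = 0.67 | 3.0 | 1.7 |
| 0.8, 0.15 | 0.1600/(0.1600 + 0.01125) = 0.93 | 15.2 | 3.9 |

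The unadjusted standard error is √(1/30 + 1/30) = 0.26 SD.

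**Step 4: bias.** Least-squares simulation: 4,000 trials per row, 30 per arm, control usage 0, intervention usage normal and clipped to 0–1, two-sided 5% level. Cells give the mean arm estimate, with the standard error and rejection rate in brackets.

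| Assumed truth | Usage mean, SD | Usage omitted | Usage entered |
|---|---|---|---|
| 0.8 SD, proportional to usage | 0.6, 0.20 | 0.79 (0.26; 84%) | −0.02 (0.63; 5%) |
| 0.8 SD, proportional to usage | 0.8, 0.15 | 0.79 (0.26; 85%) | −0.01 (1.12; 5%) |
| 0.8 SD, proportional to usage | 0.4, 0.25 | 0.80 (0.27; 82%) | −0.005 (0.41; 5%) |
| 0.8 SD, usage irrelevant | 0.6, 0.20 | 0.80 (0.26; 86%) | 0.80 (0.63; 24%) |
| 0.8 SD, usage correlated 0.4 with outcome residual | 0.6, 0.20 | 0.80 (0.26; 87%) | −0.41 (0.61; 10%) |
| No effect, usage correlated 0.4 with outcome residual | 0.6, 0.20 | 0.00 (0.26; 6%) | −1.22 (0.61; 51%) |

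The last two rows can be checked by hand. The slope of outcome on usage is 0.4 × 1/0.2 = 2, so at zero usage the line lies 2 × 0.6 = 1.2 below the arm mean. This gives 0.8 − 1.2 = −0.4 and 0 − 1.2 = −1.2. A negative correlation would shift the estimate upward by the same amount.

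**The case against.** The strongest case on the other side has five parts.

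- **The analysis is exploratory, in a pilot without a power calculation.** This stands. The primary outcomes are enrolment proportions and message opening, which do not depend on this covariate.
- **A within-arm reading is possible.** The last sentence of Exploratory Analyses speaks of comparing later values with baseline for both arms. In a model of the intervention arm alone, usage would be estimable and legitimate. But the covariate sentence is not limited in that way, and the sentence after it compares by study group.
- **Coding details may sit in a fuller document.** Coding can. Centring usage within the intervention arm and setting controls to 0 would keep the arm estimate (0.79 to 0.80 in the simulated cases with a 0.8 SD effect). The article does not specify this. The problem raised here is what it does state, that a post-randomisation variable enters the arm model.
- **Values undefined by design are not ordinary missing data, and dropping every control would be noticed.** Fair. That branch would fail visibly, so coding controls as 0 is the more dangerous one.
- **Table 1 lists usage logs at baseline, and focus groups pilot the prototype beforehand.** Nothing says that this gives a baseline usage value in both arms.

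A reader might infer that the adjusted effect is always pulled toward zero. Step 4 does not support that. It holds when the effect acts through usage; otherwise the harm is imprecision, or bias whose direction depends on how usage relates to prognosis.

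**Conclusion.** The covariate rule is wrong as written for any between-arm model. Depending on how control usage is coded, it yields no arm effect or an effect at zero usage. In the second case the standard error rises about 2.7-fold (1.7 to 3.9 over the assumed distributions). The estimate may stay unbiased, fall to about 0, or move to about −1.2 SD under a true null. That the coefficient is not the randomised contrast follows from the design unless usage has no association with outcome in the intervention arm. The sizes rest on assumed usage distributions, effect sizes and a correlation of 0.4, none of which the article gives.

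A reader might also infer that the pilot's planned effect sizes are all compromised. The document does not go that far: Power Analysis says that effect sizes will be estimated but ties them to no particular model. What can be said is that arm effect sizes taken from these models would be unusable for planning a later trial. Since the analyses are exploratory and the primary feasibility and acceptability outcomes are untouched, this should be fixed but does not threaten the trial's main purpose.

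**What to change.** In Exploratory Analyses, remove mHealth usage from the covariates of every between-arm model and state that arms are analysed as randomised. Add that the association between usage and outcome will be described separately, within the intervention arm only, and labelled non-randomised.

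The cost is a sentence or so of text and no new data. With usage omitted, 30 per arm and an assumed effect of 0.8 SD, the simulated arm estimate is 0.79 to 0.80 with a standard error of 0.26 to 0.27. Results reports baseline data only, with the texting system still being built, so at that stage the change could be made before any outcome data existed.
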